## 13.4 Conditions of Study Suspension

Suspension of the trial means that the clinical trial does not end as planned but stops during the trial. The main purpose of the trial suspension is to protect the rights and interests of the subjects, ensure the quality of the trial, and avoid unnecessary economic losses.

1. If a serious safety problem occurs during the trial, the trial should be suspended in time.
2. The effect of the drug is found too poor or even ineffective and has no clinical value during the trial, the trial should be suspended to avoid delaying the effective treatment of the subjects and at the same time to avoid unnecessary economic losses.
3. The protocol of clinical trial is found to have major mistakes and it is difficult to evaluate the effect of drugs, or a well-designed protocol has a significant deviation in the implementation, and it is difficult to evaluate the effect of drugs if continues.
4. The sponsors request the suspension (such as funding reasons, management reasons, etc.).
5. The administrative departments cancel the test, etc.

A final assessment of the subject should be made at this time and the suspension of study should be recorded on the appropriate page of the CRF. Subjects who withdraw from the trial due to adverse events should be followed up by the investigator.

## 13.5 Conditions of Study Termination

National Medical Products Administration may order the applicant to modify the trial protocol, suspend or terminate the clinical trial under any of the circumstances as follows:

1. The ethics committee fails to perform its duties;
2. Unable to effectively guarantee the safety of the subjects;
3. Fail to report serious adverse events within the prescribed time limit;
4. Evidence to prove that the drugs used in clinical trials are ineffective;
5. Quality problems of the drugs used in clinical trials;
6. Fraud in clinical trials;
7. Other violations of the Quality Management Code for Drug Clinical Trials.

# Evaluation Criteria of Efficacy

## 14.1 Observation period and index

- During infusion:

Evaluate the infusion safety of umbilical cord-derived MSCs. Observe the changes in vital signs during infusion; whether there is fever, nausea, vomiting, etc.; whether there is an allergic reaction; whether there is hemolysis; whether there is shock, and so on. Note that all AE events should be recorded and whether it is related to infusion should be determined by the investigators.

- After transfusion:

Detect platelet counts at 1, 2, 3, 4, 5, 6, 7, 8, 9, 10, 11, 12, 16, 20, and 24 weeks after 4 times infusion, and the changes in peripheral blood platelet count are recorded to evaluate the evaluation of platelet. At the same time, the safety of umbilical cord-derived MSCs is evaluated. Vital signs of the subjects, hepatitis B, hepatitis C, and other virus infections, and adverse reactions related to MSC infusions such as fever, embolism, vomiting, diarrhea, rash, and so on are observed immediately after the first infusion to the 4th month (16w).

- One week to the first month after the first infusion:

Detect the platelet count once a week and record the changes in peripheral blood platelet count. The safety of umbilical cord-derived MSCs is evaluated comprehensively during each infusion. Observe whether there are adverse reactions related to MSC infusion, such as fever, embolism, vomiting, diarrhea, rash, and so on.

## 14.2 Evaluation Criteria of Efficacy

- Main efficacy criteria:

umbilical cord-derived MSCs infusion can increase the platelet count of the subjects, indicating that the drug is effective.

Evaluation criteria of efficacy:

According to the international consensus of ITP:

- complete response (CR): platelet count ≥ 100 × 10^9^ /L and no bleeding after treatment.
- response (R): platelet count ≥ 30 × 10^9^ /L and at least doubling of the baseline count, and no bleeding after treatment.
- No response (NR): platelet count <30 × 10^9^ / L or less than doubling of the baseline count or bleeding after treatment.
- Relapse: platelet count below 30 × 10^9^/L, or less than doubling of the baseline count, or bleeding, after the achievement of CR or R.

When defining a CR or R, it should be tested at least twice with an interval of at least 7 days.

- Safety efficacy criteria:

The subjects have no obvious adverse reactions caused by umbilical cord-derived MSC infusion, normal vital signs, no hepatitis B, hepatitis C, and other virus infections, and no abnormal organ function. There was no significant difference (P > 0.05) in heart, liver, and renal function between objects before and after treatment, indicating that umbilical cord-derived MSCs have no obvious side effects and are safe.

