Traditional therapies of ITP in adults include first-line treatments (glucocorticoids with or without intravenous immunoglobulin (IVIG)) and second-line treatments (thrombopoietin (TPO), TPO receptor agonists, splenectomy, and immune-suppressive agents (such as Rituximab, Vincristine, and Azathioprine)). As one of the most common hemorrhagic diseases, ITP has a poor response to the current treatment and most patients need long-term medication maintenance treatment to alleviate bleeding symptoms, which seriously affects their quality of life and increases the economic burden on patients. Therefore, for adult ITP patients, especially refractory ITP patients, there is an urgent need for new treatments of solutions to solve this clinical dilemma. At present, some studies at home and abroad have tried to utilize the immunomodulatory function of MSCs to treat ITP patients and achieved certain effects. However, these results are all from small-sample case reports, and lack of credibility. Therefore, we designed this clinical trial to provide a definite clinical basis for the treatment of refractory ITP with UC-MSCs.

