# 5. Study Design and Statistical Methods

## 5.1 Study Design

This is a single-centre, open-label, single-arm study, which is divided into two-stage: dose-escalation stage, and dose-expansion stage.

In the dose-escalation stage, three successively increasing dose groups were set up, and the initial dose of the study was the lowest dose group. Subject enrollment, judgment and treatment of dose-limiting toxicity (DLT) refer to the traditional "3+3" dose-escalation design principle. That is, starting from the lowest dose group, 3 subjects were enrolled each time. If no DLT is observed, the trial will be continued at the next level dose; if DLT occurs in one of three patients, three more patients will be enrolled in the current dose, and when no DLT occurs anymore, the trial will be continued at the next level dose. If 2 or more DLTs occur in the 3 or 6 patients, the dose escalation will be stopped, and the current dose will be determined as the maximum tolerated dose (maximum tolerated dose, MTD). The flow of this trial is shown in Figure 1. Considering the safety of UC-MSCs, there will be 9 to 12 patients enrolled in the dose-escalation stage.

[figure not shown]
**Figure 1.** “3 + 3” dose-escalation protocol

[figure not shown]
The final dose in the dose-expansion phase will be determined based on the MTD in the dose-escalation phase, safety, efficacy, and opinion considered by the principal investigator, six patients will be enrolled in the dose-expansion stage to preliminarily explore the efficacy.

**Figure 2.** Six subjects will be enrolled to further evaluate the safety and efficacy of this dose infusion of umbilical cord MSCs

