# Inclusion, Exclusion Criteria and Assignment Methods

## 6.1 Inclusion Criteria

1. 18-60 years of age;
2. Confirmed diagnosis of ITP for at least 6 months with an insufficient response to first-line treatment drugs (IVIG, glucocorticoids), and thrombopoietic agents (recombinant human thrombopoietin (rhTPO), eltrombopag, avatrombopag, romiplostim, etc.) and anti-CD20 monoclonal antibody (rituximab) in second-line, or failed to splenectomy or subsequent relapse;
3. Subjects who received splenectomy or rituximab must have finished the therapy more than 3 months prior to UC-MSCs inclusion;
4. Platelet counts < 30×10^9^/L with bleeding;
5. Expected survival time for at least 6 months;
6. The function of liver and kidney is less than 1.5 times the upper limit of normal value, and the physical examination is qualified;
7. Subjects are allowed to maintain stable ITP concomitant treatment. The dose of glucocorticoids (less than or equal to 0.5mg/kg prednisone or equivalent dose of glucocorticoids) and thrombopoietin receptor agonists should be stable for at least 4 weeks, and the dose of azathioprine, danazol, cyclosporine A, mycophenolate mofetil, tacrolimus, and retinoic acid should be stable for at least 12 weeks;
8. Be able to understand the purpose and risks of the study and provide informed consent in accordance with national and local privacy regulations;
9. Cardiac function: Grade 2 or below according to the New York Society for Cardiac function;
10. ECOG physical status score ≤ 2.

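### The main efficacy criterion in section 14.2 infers effectiveness from an unspecified platelet rise and is not tied to the confirmed response definitions below it

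*Protocol*

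**What the plan says.** Under the label for the main efficacy criteria, Protocol 14.2 states that "umbilical cord-derived MSCs infusion can increase the platelet count of the subjects, indicating that the drug is effective". The safety criterion at the end of the section has the same form: an observed pattern is said to indicate that the product is safe.

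Between the two, 14.2 defines complete response, response, no response and relapse. Response needs a count of at least 30×10^9/L, at least twice baseline, and no bleeding. For both response categories, "When defining a CR or R, it should be tested at least twice with an interval of at least 7 days".

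The setting in which the criterion would be applied is as follows:

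- **Design (5.1):** "This is a single-centre, open-label, single-arm study, which is divided into two-stage: dose-escalation stage, and dose-expansion stage".
- **Entry (6.1):** "Platelet counts < 30×10^9^/L with bleeding".
- **Counts (14.1):** "Detect platelet counts at 1, 2, 3, 4, 5, 6, 7, 8, 9, 10, 11, 12, 16, 20, and 24 weeks after 4 times infusion". The attached flow chart schedules blood counts at W1–W16, W20, W24 and W28.
- **Other treatment:** stable background ITP drugs are allowed (6.1, 11.1, 11.2), dexamethasone precedes each infusion (9.2), and platelet-raising rescue may be given at any time (11.5).
- **Analysis (5.23):** primarily descriptive, with proportions and 95% confidence intervals for efficacy.

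**The concern.** The sentence in 14.2 is the only one in the protocol that says which data would lead to the conclusion that the product is effective. It does not say how large the rise must be, when it is measured, in how many subjects it must occur, or whether it must be confirmed. Subjects enter because their count is low, so some later counts will be higher with no treatment effect. There is no control arm against which to judge that rise, and background or rescue therapy can add to it.

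Section 5.1 lets efficacy inform the expansion dose. Section 13.4 makes lack of effect a ground for suspending the trial. The background section says that "we designed this clinical trial to provide a definite clinical basis for the treatment of refractory ITP with UC-MSCs". A criterion that an inert product could easily meet supports none of these uses.

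This is not detail that a statistical analysis plan would normally supply. The protocol states an inference that its design cannot support, and an analysis plan built on CR and R would leave that sentence standing.

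**Working it through.** **The plan's own figures.** The stated total is at least 15: three dose groups of 3 plus 6 in expansion, 3×3 + 6 = 15 (12 + 6 = 18 at the upper end of the escalation range). This reproduces. No error rate, null response rate or target rate is given for the efficacy criterion, so there is nothing further to reproduce.

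**Number of later counts, k.** Section 14.1 lists weeks 1–12 plus 16, 20 and 24: k = 12 + 3 = 15. The flow chart lists W1–W16 plus W20, W24 and W28: k = 16 + 3 = 19.

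**Any rise, inert infusion, no selection.** If baseline and the k later counts are exchangeable and ties are ignored, baseline is the highest of the k + 1 counts with probability 1/(k + 1). So P(at least one later count above baseline) = k/(k + 1).

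| | k = 15 | k = 19 |
|---|---|---|
| One subject | 15/16 = 93.8% | 19/20 = 95.0% |
| At least 8 of 15 subjects | >99.99% | >99.99% |
| All 15 subjects | (15/16)^15 = 38.0% | (19/20)^15 = 46.3% |

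**With selection at entry.** The documents give no median or SD for counts, so these are assumed and varied. Counts are log-normal with no treatment effect, and subjects enter only if baseline is below 30×10^9/L. The population median is 10, 15, 20 or 30×10^9/L, the between-subject log-SD 0.5, and the within-subject log-SD 0.2, 0.35 or 0.5. Autocorrelation between successive later counts is 0 or 0.6. There are 19 later counts; with 15 the any-visit figure would be slightly lower.

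| Reading of the criterion | Chance with an inert infusion |
|---|---|
| One subject, any visit above baseline | 92.3–99.5% |
| One subject, week 4 above baseline | 50–67% |
| Mean of 6 subjects, week 4 | 52–92% |
| Mean of 15 subjects, week 4 | 54–99% |
| Mean of 15 subjects, averaged over all visits | 57–100% |

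**Dependence on the assumed median.** At a median of 25 with (between, within) log-SDs of (0.4, 0.3), (0.5, 0.5) and (0.6, 0.4), the all-visit mean rises by chance in about 91–98% of groups of 6 and 82–92% of groups of 3. The average spurious rise is 3–7×10^9/L. At medians of 10–15 the figure for groups of 6 falls to about 55–84% (about 52–72% at week 4). The high group-mean figures therefore describe one favourable scenario.

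**Comparison with the protocol's own response thresholds.** Requiring at least 30×10^9/L and at least twice baseline at two consecutive scheduled counts, an inert infusion qualifies in 0–50% of subjects over the same grid. At medians of 15–20 with within-subject log-SD 0.35 it qualifies in about 5–15%. The no-bleeding condition is not modelled and would lower these figures. The thresholds discriminate far better than any rise, but they do not remove chance response in a single arm.

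**The case against.** The strongest reply is that the sentence is not a decision rule. The CR, R and NR definitions sit under the same bullet, so one can read the sentence as naming platelet count as the efficacy variable and the definitions as giving it content. No endpoint in 3.2 is an unqualified increase: the listed items are response rate, fixed thresholds, and at least 30×10^9/L with a two-fold rise. The re-infusion section also uses a confirmed, thresholded response. Efficacy is secondary and to be evaluated preliminarily, the analysis is descriptive, and the sentence is attached to no test, sample size or stopping boundary. The limits of a single arm are openly declared.

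Much of this stands. It lowers the severity and means that the any-rise reading is one reading among several. It does not supply the missing link: 14.2 never says that effectiveness is judged by CR or R, and no passage sets a rate that would count.

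Two stronger readings are tempting, and the documents do not support them.

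- A reader might infer that the trial's efficacy conclusion is all but predetermined. That follows only if any rise at any visit suffices, which the protocol does not state. On mean-rise readings the chance can be near a coin toss, and if all 15 subjects must rise it is 38–46% without selection.
- A reader might infer a flat contradiction, since a subject going from 10 to 14×10^9/L shows an increase yet is a non-responder. But the sentence speaks of the drug and the subjects as a group, while NR classifies one patient. The two are unconnected, not strictly contradictory.

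**Conclusion.** The point holds in limited form, at moderate severity. Section 14.2 draws a conclusion of effectiveness from a platelet rise that it leaves undefined and does not tie to its own confirmed response categories. On the literal any-rise reading, an inert infusion satisfies it in 93.8–95.0% of subjects by exchangeability alone, and in about 92–99% with entry selection under the assumed variability. On mean-rise readings the range is roughly 52–100%. The exchangeability figures need no distributional assumption; the others rest on assumed medians, SDs and autocorrelation that are not in the documents.

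Whichever reading is taken, an uncontrolled rise from a selected low count, with other ITP treatment allowed, cannot by itself show that the product works. Because efficacy is secondary and mainly descriptive, this is a faulty inference to remove, not a defect in the trial's primary purpose.

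**What to change.** In 14.2, delete the closing clause of the main efficacy criterion, which draws the conclusion of effectiveness, and replace the criterion with wording such as:

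> Efficacy is described by the proportion of subjects with confirmed CR or R as defined in this section, by dose, with a 95% confidence interval. In this single-arm study these figures describe preliminary activity only. A rise in platelet count alone will not be taken to show that UC-MSCs are effective.

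This is a wording change. It uses definitions already in 14.2 and intervals already planned in 5.23, and it alters no visit, sample or treatment. The small downside is a more modest claim.

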## 11.4 Additional Follow-up Period (> 28w):

After the end of the study, patients who have responded to MSC treatment can continue to be followed up to observe changes in platelet levels until relapse. All enrolled patients need to be followed up for a long time (> 2 years) to observe the occurrence of malignant tumors.

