# Compassionate use Regimen:

1. Applicable subjects: In this study, subjects who have no obvious adverse reactions after umbilical cord-derived MSCs infusion and respond to the treatment, if the platelet count decreases again, and is judged as relapse by the investigator, and the subjects request another infusion, umbilical cord-derived MSC infusion therapy could be given again;
2. Response (R) is defined as platelet counts ≥ 30 × 10^9^/L after MSCs treatment for at least 2 times (7 days apart), and at least doubling of the baseline count with no bleeding.
3. Relapse is defined as subjects who are judged to respond to treatment after the infusion of UC-MSCs by the investigator, and whose platelet count is found to be less than 30 × 10^9^/L again after follow-up or with bleeding.
4. The inclusion and exclusion criteria, management of infusion and concomitant medications, and emergency treatment for compassionate dosing regimen are consistent with this protocol.
5. Dose of re-infusion: the final dose used in the dose-expansion phase.
6. Infusion time: At least 16 weeks after the first infusion of UC-MSCs in this study.
7. Evaluate the efficacy and safety of umbilical cord-derived MSCs again, complete the pharmacokinetic study, detect the production of MSCs’ antibodies, and monitor the immune function;
8. Continued follow-up time: at least 16 weeks after the first dose of UC-MSC infusion in the supplemental regimen.

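### Section 14.2 confirms response with two counts but scores platelet relapse on one, so fluctuation alone can classify responders near the limit as relapsed

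*Protocol*

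**What the plan says.** Protocol section 14.2 sets four efficacy categories: CR, R, no response and relapse. Relapse is met by a count below 30×10^9/L, "or less than doubling of the baseline count, or bleeding, after the achievement of CR or R". One confirmation sentence follows, and it names two of the four categories: "When defining a CR or R, it should be tested at least twice with an interval of at least 7 days". No repeat count is stated for relapse.

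Two other places use the term.

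- Section 11.4, on follow-up beyond 28 weeks: "patients who have responded to MSC treatment can continue to be followed up to observe changes in platelet levels until relapse".
- The compassionate use section, which has its own definition. It starts from someone already judged a responder, and relapse then describes a person "whose platelet count is found to be less than 30 × 10^9^/L again after follow-up or with bleeding". That section also asks for two counts 7 days apart for a response and states none for relapse. Its relapse definition has no limb for less than doubling of baseline.

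**The concern.** Gaining a response takes two agreeing counts, while losing it on platelet grounds takes one. Every scheduled count after confirmation is a separate chance to be called relapsed, so the probability of a false label rises with the number of visits even when the true platelet level has not moved. For example, a subject with baseline 10 who shows 45, 50, 28, 52 and 55 (×10^9/L) at successive weekly visits without bleeding is a confirmed responder and also a relapse.

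At stake are the relapse proportion and any relapse-based duration of response reported from the 14.2 categories, and the point at which the long-term record of a responder stops under 11.4. With about 15 subjects in the trial, one or two misclassified responders would visibly change the picture.

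**Working it through.** The protocol states no relapse rate or error figure tied to this rule, so there is nothing to reproduce. The check is how often the rule as written mislabels a responder whose true level is constant.

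**Number of later counts (from the protocol).** The flow chart schedules counts at W1–W16, W20, W24 and W28: 16 + 3 = 19. If response is confirmed at W1–W2, 19 − 2 = 17 remain, which is the maximum. Section 14.1 lists 15 counts after the four infusions. If the first two of these confirm response, 15 − 2 = 13 remain. The flow chart after W6 also gives 10 + 3 = 13.

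**Limit (from the protocol).** The 14.2 limit is the larger of 30 and twice baseline. Entry requires a baseline below 30, so the limit lies between 30 and just under 60.

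**Chance of a spurious dip, q (assumption).** The protocol gives none. A range of 1% to 10% per count is used, with counts independent.

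**Formulas.**
- One low count among n: 1 − (1 − q)^n.
- Two consecutive low counts: let a be the probability of no pair so far with the last count not low, b the same with the last count low, and c the probability that a pair has occurred. Start at a = 1 − q, b = q, c = 0. At each further count, a becomes (a + b)(1 − q), b becomes a·q, and c becomes c + b·q. The result is c after n counts.

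Example: q = 0.05, n = 17 gives 1 − 0.95^17 = 58.2% for one count and c = 3.8% for two.

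| q | One count, n = 17 | Two consecutive, n = 17 | One count, n = 13 | Two consecutive, n = 13 |
|---|---|---|---|---|
| 1% | 15.7% | 0.2% | 12.2% | 0.1% |
| 2% | 29.1% | 0.6% | 23.1% | 0.5% |
| 5% | 58.2% | 3.8% | 48.7% | 2.8% |
| 10% | 83.3% | 13.8% | 74.6% | 10.5% |

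**Which responders are affected.** Assume log-normal variation around a constant median, with σ = √ln(1 + CV²) and q = Φ[ln(limit/median)/σ]. Example: median 50, limit 30, CV 25% gives σ = 0.246 and q = Φ(−0.511/0.246) = 1.9%. Then 1 − 0.981^13 = 22%. Simulation of 200,000 subjects per setting, with 13 independent counts, gives (one count → two consecutive):

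| Baseline | Limit | True median | CV 15% | CV 25% | CV 35% |
|---|---|---|---|---|---|
| 10 | 30 | 50 | 0.4% → 0.0% | 22% → 0.4% | 59% → 4.8% |
| 20 | 40 | 60 | 4.2% → 0.0% | 49% → 2.8% | 80% → 14% |
| 25 | 50 | 60 | 78% → 13% | 97% → 43% | 99% → 59% |
| 25 | 50 | 100 | 0.0% → 0.0% | 3.2% → 0.0% | 24% → 0.5% |
| 10 | 30 | 80 | 0.0% → 0.0% | 0.0% → 0.0% | 2.5% → 0.0% |

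Serial correlation narrows the gap. At correlation 0.5 between successive counts, baseline 20, median 60 and CV 25%, the figures are 40% → 10.5%.

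**The two relapse definitions.** At baseline 25, median 60 and CV 25%, one count under the 14.2 limit mislabels 97%. One count under the compassionate use limit of 30 mislabels 3%. The limb on less than doubling accounts for the difference.

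**The case against.** The strongest case against is that little in the trial turns on the label, and most of it stands.

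- **Endpoints.** Section 3.2 lists neither a relapse proportion nor a relapse-based duration. Its durability endpoint, the longest run of counts at or above 30, does not use the relapse definition. One low count breaks that run too, but this change would not alter it.
- **Follow-up.** A reader might infer that relapse ends a subject's platelet follow-up. It does not: the scheduled counts run to W28 for everyone, and the classification could be recomputed from them. Only the optional follow-up after W28 is tied to relapse.
- **Re-infusion.** A reader might also infer that one dip opens another course. The compassionate use section asks for more: "if the platelet count decreases again, and is judged as relapse by the investigator, and the subjects request another infusion", no obvious adverse reaction, a delay of "At least 16 weeks after the first infusion of UC-MSCs in this study", and the entry criteria again ("The inclusion and exclusion criteria, management of infusion and concomitant medications, and emergency treatment for compassionate dosing regimen are consistent with this protocol"), which include a count below 30 with bleeding.
- **Size.** The dip chance, CV, median and correlation are all assumed, and 17 counts is the maximum. This is right, which is why ranges and the 13-count case are shown. Section 13.3 does foresee response before the infusion course is complete, so early confirmation is possible.
- **Preference or SAP detail.** Counting loss of response readily is cautious in a single-arm trial, and a SAP often sets confirmation rules. But the protocol defines relapse itself and limits its confirmation sentence to CR and R, so the rule is already fixed here.

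**Conclusion.** The point holds as a defect in how one efficacy category is classified. Applied as written, 14.2 can label a stable responder near the limit as relapsed. For an assumed 1% to 10% chance of a spurious dip per count, that is about 16% to 83% of such responders over 17 counts or 12% to 75% over 13. With two consecutive low counts it is about 0.2% to 14% over 17. It is not a general property of stable responders: at baseline 10 and median 80 the one-count figure over 13 counts is 2.5% or less up to CV 35%.

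The consequences are confined to the descriptive relapse results and the optional follow-up after W28. The documents do not support the stronger inferences that listed endpoints are biased, that in-study data are lost, or that a single dip leads to re-infusion. The difference between the two relapse definitions is a separate contradiction and does not depend on any variability assumption.

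**What to change.** In section 14.2, for efficacy classification only:

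- define platelet-based relapse as two consecutive scheduled counts below the limit, dated to the first;
- count a subject as relapsed at the first low count if rescue or retreatment starts after it, or if it is the last available count;
- leave the bleeding limb unchanged;
- use the same classification for the relapse that ends follow-up in 11.4.

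This does not govern when the investigator treats.

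The cost is a short addition to the text, with no new visits. Relapse is classified one visit later, and after W16 up to 4 weeks later, although it keeps the earlier date. The last-count provision gives back part of the gain, because a chance dip at the final visit still counts. This adds the final value of b in the recursion: at q = 5% and 17 counts, 3.8% + 4.6% = 8.4%, still well below 58%.

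Separately, the sponsor must reconcile the relapse definitions in 14.2 and the compassionate use section, since only 14.2 has the limb on less than doubling. This review does not say which rule should govern re-infusion.
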